## Internal pilot

The internal pilot phase of the SCOPiC trial will assess recruitment and follow-up rates over the first 8 months of recruitment, success of GP practice recruitment and retention, success of physiotherapy site recruitment including training and engagement, adherence to the treatment protocols, suitability of the patient selection criteria, proportion of participants allocated to each of the three subgroups according to the stratification algorithm, time to magnetic resonance imaging scan (MRI) and specialist opinion for those in the fast-track pathway (subgroup 3), the event rate of the primary outcome, and rate of missing data for the primary outcome up to 4-month follow-up for all participants recruited within the 8 months of the pilot trial phase. Details of the internal pilot analysis are described under the ‘Statistical analyses’ section.

## Stratified care arm: Matched care pathways and the delivery of treatments

### Physiotherapy management in primary care

#### Subgroup 1 (STarT Back tool; Low risk)

Patients in this subgroup are expected to have a good prognosis and will receive a brief treatment package delivered by trial physiotherapists. In contrast to patients with non-specific LBP and a score of 3 or less on the STarT Back tool, patients with sciatica tend to have more severe symptoms, hence the decision to offer a referral to physiotherapy for brief treatment. Patients receive up to two 30-min sessions with the physiotherapist, with a target of delivery over 4 weeks, in order to permit review where needed but no further sessions will be offered. The package of care is tailored to the individual patient’s presentation and specific needs in order to support self-management and reduce disability. It includes advice, information, appropriate reassurance and education about sciatica. It focuses on the expected good prognosis and recovery without the need for further tests or investigations, the maintenance of activity levels including return to work where appropriate, and lifestyle advice such as general activity and weight control as appropriate as well as guidance on self-management and management of future flare-ups of sciatica. Pain relief and appropriate medication are also discussed with any suggested changes in analgesia communicated to the patient and their GP for consideration. To reinforce key messages, a sciatica booklet (developed from existing educational materials already available in the sciatica literature) will be given to the patient along with an information sheet of local contacts for exercise venues such as swimming pools, exercise classes and physical activity opportunities.

#### Subgroup 2

Patients allocated to this subgroup receive a course of physiotherapy treatment, tailored to their individual needs. This matched treatment package is delivered in an initial 45-min session with a target of up to 6 further 30-min sessions over 6 to 12 weeks. The STarT Back tool score and clinical assessment findings guide the treating physiotherapist in targeting management towards the physical and psychosocial factors that are particular problems for each patient. The physiotherapist agrees an individualised treatment plan with the patient according to their need and best current evidence. The main aims of treatment are to reduce pain, decrease disability and address modifiable physical and psychological obstacles to recovery. Management plans include some or all of the following: advice, explanation, reassurance and education, medication review and advice (with any suggestions on analgesia communicated to the patient and their GP for consideration), exercise (McKenzie ‘directional preference exercises’, strengthening-muscle stability exercises, general fitness and mobility exercises and guidance on pacing using graded activity principles depending on patient presentation), manual therapy techniques (joint and/or soft tissue), acupuncture and advice about and plans for return to normal activities and work as appropriate. Psychological obstacles to recovery, such as fear-avoidance beliefs, pain related low mood and distress or anxiety, unhelpful or erroneous beliefs about back pain and sciatica and catastrophising are also addressed as part of the physiotherapy treatment. The same sciatica booklet and information sheet of local contacts for exercise venues, as those given to patients in subgroup 1, are also given to patients in subgroup 2. Management of future flare-ups of sciatica are addressed as part of the treatment plan. Consistent with evidence based guidelines, bed rest, traction, massage and electrotherapy are not included in the treatment options [10].

The treatments for subgroups 1 and 2, are delivered in primary care by NHS physiotherapists. Participants continue to be able to access other care via their GP. The physiotherapists treating patients in subgroups 1 and 2 are responsible for providing good clinical governance to their patients and will be permitted to overrule the stratification algorithm recommendation for matched care pathways, if they strongly believe this is necessary. As in our previous trials^23^, such protocol deviations are expected to be rare and will always be discussed with the treating physiotherapist’s spinal specialist mentor and the trial principal investigator (PI), and documented.

### Fast-track care pathway to specialist spinal service

#### Subgroup 3

Patients allocated to subgroup 3 are fast**-**tracked to specialist assessment and opinion about suitability for other treatments, such as spinal injections or surgery. ‘Fast**-**track’ is defined as immediate referral from the SCOPiC sciatica clinic to specialist spinal assessment with service level agreements in place with participating NHS services to ensure that assessment will take place within 4 weeks of the patient’s SCOPiC sciatica clinic appointment. An MRI scan is part of the specialist spinal assessment for the patients in the ‘fast**-**track’ care pathway. A report on the MRI scan will be provided by a consultant radiologist, as per normal NHS clinical practice. The spinal specialist has access to the MRI results, as part of their assessment of patients in this ‘fast**-**track’ pathway. It is important to note that the ‘fast**-**track’ pathway is to *specialist assessment and opinion* and not to surgery or injection. Patients with contraindications to MRI see the spinal specialist who will decide on alternative imaging tests as necessary. The specialist, in discussion with the patient, determines the most appropriate treatment based on assessment and MRI findings and patient preference.

These spinal specialist services within the participating NHS services, include specialist clinics at the primary/secondary care interface (usually delivered by extended scope spinal physiotherapy specialists), spinal orthopaedic and pain clinic teams. The first appointment with specialists for patients allocated to the ‘fast-track’ pathway is at the primary / secondary care interface. These NHS services are delivered by specialist spinal physiotherapists (extended scope practitioners), any referrals to other spinal specialist services (orthopaedics, neurosurgery or pain clinic) are decided as part of routine care at this point.

#### Non-stratified care and its delivery

The control arm of the SCOPiC trial is based on non-stratified primary care, delivered by physiotherapists. Patients randomised to the control arm are treated by a physiotherapist in the SCOPiC sciatica clinic. For these patients, treatment includes a one**-**off session (in the same clinic visit) of advice and education. The treating physiotherapist then decides whether the patient should be discharged back to the care of their GP or be referred for community physiotherapy or to specialist spinal services. If an onward referral is required this is arranged by the physiotherapist at the clinic.

As previously mentioned, in order to avoid contamination between the stratified care arm and control arm, at the SCOPiC clinic, different physiotherapists provide treatment for patients in each of the two trial arms and the physiotherapists who are providing treatment to control care patients are unaware of the details of the stratification algorithm and individual participants’ group status.

#### Training for participating physiotherapists

Participating physiotherapists will attend training workshops with the trial team prior to the start of patient recruitment and treatment. Those delivering the one-off treatment for patients in the control arm in the SCOPiC clinic, will take part in a half-day workshop about trial procedures, importance of avoiding contamination between trial arms and the completion of trial CRFs.

Those involved in the stratified care arm of the trial will attend three days of training. The focus of the training will be on carrying out the standardised assessment according to agreed protocols to identify patients with sciatica for participation in the trial, the stratification algorithm, taking informed consent, the delivery of evidence based physiotherapy interventions in line with the biopsychosocial model of care and the procedures of the trial, avoiding contamination between trial arms, and the completion of trial CRFs.

The training will be supplemented by comprehensive written material on the trial procedures, and on guidelines and treatment algorithms for the evidence based assessment and treatment of patients with sciatica. To maximise protocol fidelity, physiotherapists treating patients in subgroups 1 and 2, will have support as required, this will be provided by the research team’s spinal physiotherapy specialists from the spinal services participating in the trial.

## Outcome measures and data collection

### Primary outcome

The primary outcome measure is time to first resolution of symptoms of sciatica, measured on a 6-point ordered categorical scale: ‘completely recovered’, ‘much better’, ‘better’, ‘same/ no change’, ‘worse’ and ‘much worse’ – the anchor being against the patients’ baseline symptoms when they attended the SCOPiC sciatica clinic (“compared to how you were at the SCOPiC clinic X weeks/months ago, how are your back and leg symptoms today?”). Patient-reported resolution of symptoms is defined as a response of either ‘completely recovered’ or ‘much better’, collected using regular text messages (or brief phone calls where text messaging is not possible). Data collection for the primary outcome occurs weekly, starting on the first Sunday following the participant’s assessment at the SCOPiC sciatica clinic, for the first 4 months for all participants. Then between 4 and 12-month follow-up, the text message data collection changes to once every 4 weeks, or until ‘stable resolution’ of symptoms, which is defined as 2 consecutive months’ responses of ‘completely recovered’ or ‘much better’. After stable resolution, data collection for the primary outcome via text message ceases. 94% of UK adults have a mobile phone (https://www.ofcom.org.uk./facts) and previous research has shown that weekly text messages are a useful method of data collection to examine the clinical course of back pain in primary care, with high mean response rate of 83% [30]. Participants who do not respond to their first week’s text message receive a reminder message 48 h later, and those who still do not respond are mailed a postcard the next day. Participants who do not respond to the second week’s text message receive a reminder message 48 h later, and those who still do not respond receive a phone call from a research nurse after at least a further 24 h. For subsequent non-response the reminder processes described is repeated. If the participant continues not to provide a response using text message there is an option to transfer to data collection by brief phone call.

### Secondary outcomes

Secondary clinical outcomes evaluate health status at 4 and 12 months using participant self-completed postal questionnaires with postal reminders and minimum data collection over the telephone, by research nurses. A text message is sent to participants at 4 and 12-month follow-up to notify them that the SCOPiC follow-up questionnaire will soon arrive in the post. Measures include Global Perceived Change ((GPC) (6-point Likert scale as per the primary outcome data collection)), physical function limitations (sciatica version of the Roland and Morris Disability Questionnaire) [31], overall impact of sciatica symptoms (Sciatica Bothersomeness Index) [32], pain intensity of back and leg pain [33], sleep disturbance (Jenkins sleep questionnaire) [34], fear of movement (Tampa Scale of Kinesiophobia) [35], anxiety and depression (Hospital Anxiety and Depression Scale) [36], risk of poor outcome according to the STarT Back tool [25], health related quality of life (EQ-5D-5L) [37], general health (SF-1) [38], neuropathic pain using the S-LANSS (self-report Leeds Assessment of Neuropathic Symptoms and Signs) [39], days lost from work and productivity loss due to sciatica, pain medication, adverse events and satisfaction with care received and its results. See Table 1 presents an overview of procedures and measures used according to the SPIRIT statement (Chan et al. [40]).

**Table 1 Tab1:**
[figure not shown]
Overview of enrolment, interventions, and assessments

*The interventions and their delivery are described in detail in the manuscript. Treatments are tailored to the individual participant and likely to have different frequency and duration for each participant. Overall, treatment for most participant is expected to be completed within 4 months from randomization

^**a**^ The trial’s primary outcome is time to symptoms resolution. Data collection with text messages for the primary outcome occurs weekly for the first 4 months for all participants. Between 4 and 12-month follow-up, the text message data collection changes to once every 4 weeks, or until ‘stable resolution’ of symptoms, which is defined as 2 consecutive months’ responses of ‘completely recovered’ or ‘much better’. After stable resolution, data collection for the primary outcome via text message ceases

^**b**^ At 4 and 12 months follow-up, data collection is via postal questionnaires

^**c**^ Participants and clinicians are asked to report any adverse and/or serious adverse events. Patients are asked about adverse events in the follow-up questionnaires

^**d**^ Global perceived change is collected via text messages or telephone calls, and in the follow-up questionnaires at 4 and 12 months

### Process outcomes

Process outcomes are collected to investigate the impact of stratified care on service delivery. Numbers and proportions of patients in each arm of the trial receiving appropriate referrals and treatments according to their subgroup allocation, and the timing of starting treatment, are collected from CRFs, patient questionnaires and record reviews from participating NHS services.

### Health economic outcomes

Health economic outcomes are collected to determine the costs of the interventions (stratified care and control) and other sciatica-specific healthcare utilisation. Resource use information is obtained on primary care consultations (GPs and other HCPs in the practice), secondary care consultations (e.g. hospital consultants), prescriptions, hospital based procedures (diagnostic tests, injections), nature and length of inpatient stays, surgery and over-the-counter purchases by patients. Patients are asked to distinguish between UK NHS and private provision. Cost data are collected via participant questionnaires at 4 and 12 months. If hospital records data on sciatica-related surgery or injections (to supplement patient-reported data) can be obtained, this data will be included in a sensitivity analysis. Unit costs are obtained from standard sources including the British National Formulary (BNF) [41], Unit Costs of Health and Social Care [42] and NHS Reference costs. Information is also collected from participants about their occupational status, sciatica-related time off work and reduced work performance (presenteeism) [43], to enable the calculation of productivity costs, allowing analysis from a societal cost perspective. The average wage for each respondent will be identified using UK Standard Occupational Classification coding [44] and annual earnings data for each job type [45]. The analysis will use the human capital approach, and the self-reported days of absence will be multiplied by the respondent-specific wage rate. The outcome of interest for the economic analysis is quality-adjusted life years (QALYs) and these will be calculated using EQ-5D-5L responses obtained at baseline, 4 and 12 months.

## Adverse events

Information is collected on adverse events (AEs) experienced by trial participants and potentially related to trial interventions or procedures. Physiotherapists treating patients in the SCOPiC trial are asked to report potential AEs by the use of CRFs or report to the trial team. Patients are asked about AEs in the follow-up questionnaires. Expected AEs include for example a transient increase in pain as a result of a new exercise programme. Any serious adverse events (SAEs), defined as an event that is life threatening, results in death, unscheduled hospitalisation, or significant disability, is immediately reported to the trial team according to the procedures described in the Keele CTU standard operating procedures for SAEs. Any SAEs considered to be related to the trial procedures or interventions will be reported to the main Research Ethics Committee by the Chief Investigator within 15 days of becoming aware of the event. In addition, all such events will be reported to the trial sponsor, Trial Steering Committee (TSC) and Data Monitoring Committee (DMC).

## Qualitative study

The aim of the linked qualitative study is to understand the acceptability of the ‘fast-track’ pathway in the stratified care arm of the trial, to patients and clinicians. Qualitative research on patients’ experiences of sciatica and its management is scarce [46, 47], especially in those with most severe symptoms, and qualitative studies that report clinicians’ views of managing this condition are even less common [48]. In the SCOPiC trial stratified care arm the ‘fast-track’ pathway to spinal specialist assessment and opinion is novel, and the focus of the qualitative study is on patients in this subgroup and the clinicians involved in their management.

A purposive sample of patients randomised to the stratified care arm and who are on the ‘fast-track’ pathway will be invited for interview based on treatment centre and patient demographics including age, gender, baseline leg pain severity/disability, and also response to treatment. Interviews will be conducted after the 4 month follow-up point.

Potential interviewees will be sent an invitation letter with an information leaflet about the interview, following which a researcher will contact them by phone, and arrangements made with those who agree to participate. Consent will be obtained at the start of the interview, either in writing if the interview is face-to-face, or audio-recorded if the interview is over the telephone. A semi-structured topic guide will be developed, exploring patients’ views of their clinical care, its appropriateness and timeliness for addressing their problem, and the time taken to assessment, treatment (s) and symptom resolution. Patients’ experience of sciatica symptoms and their impact will also be explored to provide context in terms of treatments received. Participating spinal specialist clinicians (spinal physiotherapy specialists, spinal surgeons), and a sample of participating GPs will be invited for interview after the trial finishes participant recruitment. Again, using a semi-structured topic guide, the interviews will explore clinicians’ views about the acceptability of the ‘fast-track’ pathway, the suitability of patients on this pathway, and explore how the ‘fast-track’ pathway compares with usual care, what the added value of the ‘fast-track’ pathway might be for this subgroup of sciatica patients, and what, if any, limitations there might be. In interviews with GPs we will also explore their perceptions of whether their involvement in the trial contributed to changes in their referral decisions for patients with sciatica. The same invitation and consent process as described above for patients will be followed with the clinicians. We estimate that sufficient data saturation [49] will be reached with a sample of 20 to 25 patients’ and clinicians’ interviews (total of approx. 40 to 50 interviews).

## Statistical analyses

The trial analysis will be conducted and reported following the Consolidated Standards of Reporting Trials (CONSORT) guidelines [50–52].

### Clinical outcomes analysis

#### Primary analysis

The primary analysis will compare time to self-reported resolution between stratified care and non-stratified care, on an intention-to-treat basis. A Kaplan-Meier survival analysis will estimate the time from randomisation until first resolution of symptoms. Participants who drop out of the trial through active withdrawal will be censored at the time this occurs (by contrast, participants not responding at any time point will continue to be followed-up until they actively withdraw). This will provide the data for comparing the relative mean and median survival times of the two trial arms. A Cox proportional hazards regression analysis will compare time to resolution between arms by calculation of a hazard ratio (HR) of rates of resolution adjusted for centre, patient stratification group (subgroups: 1, 2, 3) and baseline pain duration. The HR will be presented along with a 95% confidence interval for the HR; a p-value < 0.05 (two-tailed) based on the Wald test statistic will signify rejection of the null hypothesis of no difference in recovery time between the two arms. A statistically significant p-value with HR > 1 would indicate statistically significant shorter time to recovery for stratified care compared to control; a statistically significant p-value with HR < 1 would indicate a (statistical) significantly longer time to recovery for stratified care compared to control. The analysis will account for physiotherapist effect (proportional Cox hazards frailty model).

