## Background

About 60% of patients with low back pain (LBP) report pain in the leg (s) [1] although not all will be diagnosed as having sciatica. Sciatica is a common variation of LBP presenting with radiating pain in the leg and often accompanied by variable neurological changes in sensation, reflex or muscle strength in the leg [2]. The most common reason for sciatica symptoms is a disc prolapse compressing or irritating a spinal nerve root [2]. Sciatica prevalence estimates vary widely from 1.2 to 43%, a variation that is related to using different diagnostic criteria and sampling methods [3]. It is believed that many patients with sciatica have a favourable outcome and experience resolution of symptoms within 12 weeks from onset [2, 4]. However, a substantial proportion (estimated at up to 30%) continues to suffer with pain for a year or more [2]. Studies from primary and secondary care show that recovery after one year is moderate, varying from 49 to 58%, depending on the definition of recovery [5, 6]. The literature indicates that compared to LBP alone, sciatica has a more substantial impact on patients, with longer pain episodes [7], it is also responsible for a large proportion of the indirect costs and days lost from work associated with LBP. A Dutch study estimated that the cost of sciatica to society represents 13% of all LBP related costs [8], which translates to an annual impact to the UK economy of £268 million in direct medical costs and £1.9 billion in indirect costs.

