#### Exploratory subgroup analyses

A small number of re-analyses of the primary endpoint analysis of time to resolution will be carried out to include testing the effectiveness of stratified care for those with/without suspected disc-related radicular pain as determined by clinical assessment, and for patients in each of the stratification subgroups (subgroups 1, 2 and 3). Descriptive statistical summaries will be provided through mean/median time to resolution per treatment arm and per patient subgroup (subgroups 1, 2, 3) according to suspected/not suspected disc-related radicular pain. Tests of statistical significance will be through evaluation of 95% interval estimates / p-values for the interaction term for the product of group variable (with/without suspected disc-related radicular pain) by treatment arm within the Cox regression model adjusting for centre, stratification group (stratifying variables), and pain duration.

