## Sample size

We have calculated a sample size of 470 participants in total, in order to test for superiority of stratified care compared to non-stratified care. The primary outcome of interest in the SCOPiC trial is time to resolution of symptoms (defined as patient self-report of being ‘completely recovered’ or ‘much better’ compared to baseline (from the 6-point ordinal GPC scale). In our previous trial of stratified care for LBP [23], nearly 60% of patients in total had a clinically important improvement on the GPC scale at 4 and/or 12-month follow up; the absolute difference between arms of that trial at 4 months was 11%. If proportional hazards are to be assumed (i.e. in this case assumed relative rate of ‘resolution’), this difference would equate to an HR in the interval 1.4 - 1.5. Allowing for 20% dropout, a sample size of 470 (235 per treatment arm) is required to detect an HR between 1.4 - 1.5 with 80-90% power (given a two-tailed significance level of 5%), assuming a rate of resolution in excess of 60%, and intra-class correlation (ICC) for physiotherapist effect less than 0.01 (based on estimates from other primary care trials [23, 53], and allowing for a coefficient of variation in physiotherapist cluster size of 0.65 [54]; specifically:an HR of 1.4 in median survival times with 90% power (if all participants in the trial are recovered by 12-month follow-up and ICC for therapist effect is <0.001) (least conservative)an HR of 1.5 in median survival times with 80% power (if 60-65% of participants in the trial are recovered by 12-month follow-up and ICC for physiotherapist effect is 0.01) (most conservative)

An HR above 1 (and correspondingly lower ‘survival’ function) in this context is a positive result in contrast to traditional survival analysis of mortality.

This sample size will also provide more than 80% power to detect a ‘small’ to ‘moderate’ standardised mean difference (effect size) of 0.35 [55] between the two trial arms in a key secondary outcome of physical disability at 12-month follow-up, allowing for an ICC for physiotherapist effect of 0.01.

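### Mean time to resolution is planned from Kaplan-Meier curves with no time horizon, although follow-up ends at 12 months with up to 35-40% expected to be unresolved

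*Protocol article*

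**What the plan says.** Under Primary analysis the protocol article states: "A Kaplan-Meier survival analysis will estimate the time from randomisation until first resolution of symptoms". It then adds: "This will provide the data for comparing the relative mean and median survival times of the two trial arms". The decision rule in the same section is separate: a Wald test on the adjusted Cox hazard ratio at the two-sided 5% level.

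Under Exploratory subgroup analyses the mean returns: "Descriptive statistical summaries will be provided through mean/median time to resolution per treatment arm and per patient subgroup" (subgroups 1, 2 and 3), further split by suspected or not suspected disc-related radicular pain.

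Neither section limits the mean to a period. Follow-up for the primary outcome is limited, however. Replies are collected weekly for 4 months, and the Primary outcome section continues: "Then between 4 and 12-month follow-up, the text message data collection changes to once every 4 weeks".

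The Sample size section brackets the proportion resolved. The least conservative case holds "if all participants in the trial are recovered by 12-month follow-up", and the most conservative holds "if 60-65% of participants in the trial are recovered by 12-month follow-up". The Background says of earlier studies that "recovery after one year is moderate, varying from 49 to 58%, depending on the definition of recovery".

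**The concern.** A mean survival time is the area under the whole survival curve. If the Kaplan-Meier curve is still well above zero when observation stops, the area beyond that point is unknown and the mean is not identified. The plan's own conservative assumption puts the trial in that position.

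Software will usually still print something called a mean, cut at the largest observed time or at the largest event time. That number is a truncated mean. Reported without its horizon, it can be read as the average time to recovery, which it is not. If the cut is set at the last event, it can also fall at different times in different groups.

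Means and medians are the planned summaries of the primary outcome on the time scale. They would matter more if proportional hazards failed, because the stated fallback under Assumption checking is an unadjusted log-rank test, which gives no effect size.

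**Working it through.** **1. The plan's own figure.** The sample size of 470 reproduces without using any mean. After 20% dropout, 470 × 0.8 = 376 participants remain. With Schoenfeld's formula, 1:1 allocation and two-sided 5%:
- HR 1.4, 90% power, all recovered: 372 events, so 372 / 0.8 = 465.
- HR 1.5, 80% power, 60% recovered: 191 events, so 191 / 0.60 / 0.8 = 398 before clustering. Reaching 470 implies a design effect of 376 × 0.60 / 191 = 1.18.
- The same with 65% recovered: 191 / 0.65 / 0.8 = 367, and an implied design effect of 376 × 0.65 / 191 = 1.28.

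**2. Unresolved at 12 months.** 100% − 65% = 35% and 100% − 60% = 40%. In the all-recovered case the figure is 0%.

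**3. What the mean needs.** Mean = area under S(t) from 0 to 12 months + S(12) × mean residual time after 12 months. The first term is observed. The last factor is not.

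**4. Size.** Assumptions: exponential times, HR 1.5, equal arms, 60% resolved overall.
- Solving 1 − ½[exp(−12λ) + exp(−18λ)] = 0.60 gives λ = 0.0622 per month for control and 0.0934 for stratified care.
- S(12) = 0.474 (control) and 0.326 (stratified).
- Restricted mean = (1 − S(12)) / λ = 8.45 and 7.22 months; the difference is 8.45 − 7.22 = 1.23 months.

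Now add S(12) × residual time, taking the residual as equal in both arms (a further assumption):

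| Residual after 12 months | Control mean | Stratified mean | Difference |
|---|---|---|---|
| 6 months | 11.30 | 9.17 | 2.13 |
| 12 months | 14.14 | 11.13 | 3.01 |
| 24 months | 19.83 | 15.05 | 4.78 |
| 48 months | 31.20 | 22.87 | 8.33 |

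All four rows agree with the same 12-month data. With 65% resolved overall, the restricted means are 8.06 and 6.75 months (difference 1.31), and the control mean runs from 10.60 to 28.41 months over the same residuals.

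**5. Medians.** Median = ln 2 / λ. With 60-65% resolved overall this gives 9.7-11.1 months for control and 6.5-7.4 months for stratified care. Both fall within follow-up.

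**6. Does the cut-point differ between groups?** Take 55% of controls resolved and HR 1.5. This is 1 − ½(0.45 + 0.45^1.5) = 62.4% resolved overall, inside the plan's range. The control rate is −ln(0.45)/12 = 0.0665 per month, and about 2.9% of each arm resolve in the last 4 weeks.
- Whole arm, 376 / 2 = 188 patients: about 5.4 events expected in that interval. The chance of none is about (1 − 0.029)^188, or 0.4%.
- Subgroup cells: 2 arms × 3 subgroups × 2 disc categories = 12. With equal cells (assumed), 470 / 12 is about 39 patients, or 31 after dropout. The chance of no event in the last interval is about 32% to 41%.
- If the mean is cut at the last event, losing that interval removes 0.43 months from a control mean. The 12-month restricted difference in this scenario is 8.27 − 6.99 = 1.28 months, so the loss is about a third of it.

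**The case against.** The strongest reply is that this is a condensed article, that a truncation point is normal content for an analysis plan, and that standard software already reports a truncated mean. For the whole arms this largely stands as a matter of harm. Everyone has the same 12-month schedule, non-responders stay in follow-up and count as unresolved, and many participants in each arm would still be under observation at about 12 months. The default figure would be close to the 12-month restricted mean. The reply does not remove the point, because the text names a mean and gives it no horizon. An analysis plan could supply one, but then the quantity analysed would be a different one from that named here.

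Some stronger readings are tempting but are not supported:
- **That the trial would report a greatly inflated difference.** Exponential extrapolation of the 55% scenario gives means of 15.0 and 10.0 months, a difference of 5.0. The protocol proposes no such extrapolation, and a Kaplan-Meier procedure would not produce those values from 12-month data.
- **That 42-51% will be unresolved and the control median will be missed.** These percentages are the complement of the Background's 49-58%, which rests on other studies' definitions of recovery. The endpoint here is a first single reply of much better or completely recovered, so a later relapse does not undo it. A control median of 12.4 months follows only from 49% of controls resolved, and the sample-size section assumes more than 60% resolved.
- **That the arms would be compared over different horizons in the main analysis.** The 0.4% chance above shows this is unlikely. The risk lies in the small exploratory cells, and only if the cut is at the last event.

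**Conclusion.** The point holds for the mean alone. The plan names an unrestricted mean time to resolution that its design cannot estimate unless essentially everyone recovers by 12 months. In its most conservative case, 35-40% do not. For the whole arms the practical fault is mainly one of labelling: a figure near 8.45 against 7.22 months would be called a mean when it is a mean over 12 months. In the subgroup cells the fault can also affect comparability.

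The consequence stops at the absolute-scale summaries. A reader might infer that the primary analysis is compromised. It is not: the hazard ratio, the Wald test and the 470 do not use the mean.

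The proportion unresolved comes directly from the protocol. The sizes in months rest on an exponential shape, HR 1.5, equal residual times in both arms and equal subgroup cells. The failure of identification rests on none of these. The change is worth making, but the primary inference does not depend on it.

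**What to change.** In Primary analysis and in Exploratory subgroup analyses, replace the mean with the restricted mean time to resolution over 0-12 months (52 weeks). Use the same horizon for both arms and all subgroups, and label it as restricted wherever it is reported. Report medians only where the curve reaches 50%.

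A 95% confidence interval for the between-arm difference in restricted means, in the main comparison, is a useful optional addition. It would give an effect size on the time scale if proportional hazards failed and only the log-rank test remained.

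The cost is about one sentence in each section and a standard procedure. No new data are needed, and the primary test and sample size do not change.
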